## 1. THE PROBLEM

One in three children wheeze prior to their third birthday; almost 50% of children wheeze by 6 years of age . Between 1996 and 2005, while Ontario emergency department (ED) visits for asthma decreased, the ED visits for children 0 to 4 years did not change (14.6 visits / 100 asthma individuals in 1996 versus 14.4 visits / 100 asthma individuals in 2005; *Figure 1*). Children aged 0-4 years also had the highest asthma admission rates in Ontario. Preschool children who wheeze use 0.15% of the total healthcare budget in the UK .

**Preschool wheeze represents significant morbidity for the individual and a significant burden to society.**

Preschool children who wheeze represent a number of heterogeneous populations and disorders including: 1) the majority of children who will only wheeze with viral infections and only in childhood (episodic wheeze) 2) children who will wheeze due to multiple triggers (a potential pre-cursor phenotype of asthma) and 3) children who wheeze secondary to upper airway infections such as rhino-sinusitis. These multiple, overlapping etiologies are difficult to distinguish and make the acute and chronic management of children with preschool wheeze challenging . **Many current drug therapies target inflammation as a potential cause of preschool wheeze but do not address atypical bacterial infection as a potential contributing factor to the observed morbidity.**

## 2. OVERALL AIM

We hypothesize that the addition of azithromycin, a macrolide antibiotic with anti-inflammatory  and anti-bacterial  properties, to routine therapy of wheezy pre-school children – regardless of aetiology - will resolve respiratory symptoms more rapidly, reduce the need for rescue medications in the subsequent three weeks, and protect against symptom reoccurrence longer than the addition of placebo.

To test this hypothesis, **we propose a double-blind, randomized control trial (RCT) of 5 days of azithromycin versus placebo in preschool children (between 12 and 60 months of age) presenting to the pediatric ED with wheezing symptoms.**

## 3. BACKGROUND LITERATURE

**Challenges in managing preschool wheeze:** While many physicians label preschool children with recurrent wheeze as having asthma, some experts now distinguish two patterns of disease: episodic and multiple-trigger wheeze . Episodic wheeze is defined as wheeze in discrete episodes, with the child being well between episodes. Although not unique to the preschool age group , this phenotype appears to be most common in preschool children . Multi-trigger wheeze is defined as those children who have persistent respiratory symptoms in between acute wheezing episodes. These children's symptoms are triggered by multiple triggers such as allergens, exercise, and cold air. Unfortunately, a viral respiratory tract infection is the most common trigger factor for wheeze in preschool children regardless of the episodic or multiple trigger classification . This makes it difficult to distinguish children who wheeze due to multiple-triggers from those children with episodic wheeze.

In addition to episodic and multiple-trigger wheeze, some experts believe a child's response to treatment with their first episode of wheeze (bronchiolitis)  is different than if

they had a prior episode of wheeze. Others believe that a child's response to treatment with their first wheeze is likely to be heterogeneous, and more dependent on whether they have an intrinsic predisposition to have episodic or multiple-trigger wheeze. Current evidence is insufficient to determine if either or both views are true.

In addition to episodic, multiple-trigger, and first-time wheeze, co-morbid conditions such as rhino-sinusitis may contribute to wheeze symptoms. The presence of chronic rhinitis and sinusitis is frequently diagnosed in children with asthma. Treatment of the upper airway conditions in patients with asthma improves the function of the lower airway, although the mechanism by which lower airway function improves remains theoretical. Potential mechanisms by which rhino-sinusitis may influence preschool wheeze include a combination of systemic inflammatory signals, breathing mechanics, or bacterial contaminants from the upper airway entering the lung.

**Aetiology and pathophysiology:** A recent European Respiratory Society (ERS) taskforce concluded that the pathogenesis of pre-school children who wheeze has been inadequately studied, and that many preschool children who wheeze may not have the classic inflammatory changes characteristic of older children and adults with asthma. Preschool wheeze is usually associated with clinical evidence of a viral respiratory tract infection. The most common infectious agents include rhinovirus, respiratory syncytial virus (RSV), coronavirus, human metapneumovirus, parainfluenza and adenovirus. It is unclear what role bronchospasm and bronchial smooth muscle hyperreactivity play versus airway inflammation, edema and accumulation of debris in the development of clinical signs of wheeze. Few studies have investigated the presence of airway inflammation in preschool wheezy children. Elevated exhaled nitric oxide fractions ( $F_{eNO}$ ), an indirect marker of airway inflammation, have been found in wheezing infants, especially when they are atopic, and  $F_{eNO}$  levels normalise during treatment with inhaled corticosteroid (ICS) or leukotriene receptor antagonists (LTRA) such as montelukast.

**Pharmacological therapy:** The current management of children who wheeze includes supplemental oxygen, hydration and nutrition. Inhaled short acting  $\beta_2$ -agonists (SABA) are the drugs of choice for acute symptoms of wheeze. RCT of SABA in infants and preschool children have demonstrated significant bronchodilator effects and protective effects against broncho-constrictor agents. While SABA are effective acutely, they require frequent administration and do not influence the underlying disease pathogenesis.

Systematic reviews are available that evaluate the utility of ICS, LTRA or long acting beta-agonists (LABA) to treat children with asthma. Preschool wheeze may not represent the same pathophysiology as asthma and the role for these drugs to treat preschool wheeze may be different. Several studies have examined the role of ICS and LTRA to modify the underlying disease pathogenesis (presumed inflammation and airway hyperreactivity) of wheezing preschool children. There have been no trials of LABA or macrolides for the acute treatment of preschool wheeze.

**ICS and oral corticosteroids:** The benefits of ICS may depend on whether children wheeze episodically or whether they wheeze in response to multiple triggers. A recent meta-analysis demonstrated improvement in wheezing symptoms and time to next wheeze/asthma exacerbation in preschool children with recurrent wheeze treated for 4 to 6 weeks with ICS. The benefits of ICS for episodic wheeze are more controversial. Systematic reviews have concluded that episodic high-dose ICS results in a 50% reduction in the requirement for oral steroids but without an effect on hospitalisation rates or duration of symptoms. The most

recent study showed that intermittent treatment with high dose ICS at the start of a respiratory tract infection (RTI) reduced the severity and duration of symptoms but at a cost of reduced height and weight gain. Maintenance treatment with low-dose ICS does not appear to reduce the number or the severity of wheezing episodes in episodic (viral) wheeze. Similar results were found with the use of oral prednisolone in preschool children with episodic wheeze who present to a hospital. A systematic review of two studies found no evidence that parent-initiated oral corticosteroids are associated with a benefit in terms of hospital admissions, unscheduled medical reviews, symptoms scores, bronchodilator use, parent and patient impressions, physician assessment, or days lost from work or school. As it is difficult to distinguish children with episodic versus multiple-trigger wheeze, treating all wheezing preschool children with corticosteroids would treat those with episodic wheeze (the majority) with a drug that may not be effective and can have adverse effects.

**Nasal corticosteroids:** A randomised controlled trial of nasal corticosteroids in preschool children with recurrent wheeze failed to demonstrate any benefit.

**LTRA:** Daily use of Montelukast over a 1-yr period reduced the rate of wheezing episodes among 2 to 5 year old children by 32% compared to placebo (number needed to treat 12). Montelukast started when patients developed signs of a RTI also showed a 30% reduction in unscheduled health visits (number needed to treat 11), but no effect on hospitalisations, duration of episode, and SABA and prednisolone use. We have shown that Montelukast taken daily for 45 days over the period of the September epidemic reduces unscheduled physician visits by 78% compared to placebo (number needed to treat 10). While LTRA have been shown to be effective in preschool children clinically and in reducing airway inflammation, LTRA lack anti-bacterial properties which may be important in the management of wheezing preschool children.

***Macrolide antibiotics in the management of preschool wheeze:*** Macrolide antibiotics (e.g. clarithromycin, azithromycin) demonstrate anti-inflammatory effects in animal and human studies. Macrolides may reduce airway inflammation by reducing airway mucus secretion and decreasing airway neutrophil accumulation through a reduction in both pro-inflammatory cytokines and adhesion molecule production. A Cochrane review of macrolide therapy in chronic asthma management showed significant differences in eosinophilic inflammation and symptoms. In a randomized control trial of adults with severe, refractory asthma, clarithromycin significantly reduced airway concentrations of interleukin (IL)-8, metalloproteinase (MMP)-9, neutrophil elastase, neutrophil numbers, and improved quality-of-life scores compared with those adult asthmatics on placebo. In a mouse model of allergic asthma, azithromycin attenuated ovalbumin-dependent airway inflammation. While we could not identify any RCT of macrolide antibiotics in preschool wheeze with clinically relevant outcomes, macrolide antibiotics have been tested in several other pediatric respiratory diseases.

**Chronic rhino-sinusitis:** Macrolide treatment of chronic rhino-sinusitis has shown significant improvement in a variety of outcomes at 3 and 12 month follow.

**RSV Bronchiolitis:** A RCT of clarithromycin for 3 weeks in 21 infants with RSV bronchiolitis showed a significant reduction in length of hospital stay, duration of supplemental oxygen, need for SABA, and readmission to the hospital within 6 months after discharge. Infants treated with clarithromycin also showed significant decreases in plasma IL-4, IL-8 and eotaxin levels. Inclusion of children who present with first-time wheeze (i.e. bronchiolitis) will allow us to expand on the preliminary results of this study.

**Acute asthma exacerbations:** A RCT of clarithromycin in 4 – 17 year old children (n=43) with an acute exacerbation of either recurrent wheezing or asthma showed significantly lower nasopharyngeal concentrations of TNF- $\alpha$ , IL-1 $\beta$ , and IL-10 up to 8 weeks after treatment. Unfortunately all children were treated with systemic steroids and symptom outcomes were not reported. Adults with an asthma exacerbation treated for 10 days with telithromycin showed a significant reduction in asthma symptoms and improvement in pulmonary function at the end of treatment. While symptom free days continued to improve, differences in pulmonary function were not sustained at 6-week follow-up.

The efficacy of macrolide antibiotics on acute wheezing symptoms may depend on the presence of atypical bacterial infection (*Mycoplasma pneumoniae* or *Chlamydia pneumoniae*). Atypical organisms have been associated with exacerbations of asthma in both children and adults. A case control study of children (age 2 to 14 years) with an acute wheezing episode (n = 71) showed that *M. pneumoniae* and *C. pneumoniae* infections were detected significantly more often in children with wheezing symptoms than in healthy controls. During a 3-month follow-up period, those children with *M. pneumoniae* or *C. pneumoniae* showed a significantly greater recurrence of wheeze than those without atypical bacteria present. *C. pneumoniae* or *M. pneumoniae* was found in 53% of patients in the pediatric clarithromycin and asthma trial. In the adult, acute asthma exacerbation RCT, although 61% of the study population that used telithromycin had evidence of *C. pneumoniae* or *M. pneumoniae*, bacteriological status was not related to telithromycin response. However, many respiratory pathogens are not detected or are easily overlooked by routine clinical microbiology. These studies suggest that macrolide antibiotics may have an important role in the management of wheeze in children.

**Potential adverse events associated with macrolide use:** Macrolide antibiotics have been associated with significant effects on cardiac conduction, increased antimicrobial resistance, and an increase in liver enzymes among those who have abnormal liver enzyme levels prior to treatment. Statin-induced myopathy has been reported with concurrent clarithromycin therapy.

Macrolide antibiotics possess pro-arrhythmogenic effects leading to prolong cardiac repolarisation and potentially fatal ventricular tachycardia. The risk is increased five-fold if patients are concurrently taking cytochrome P4503A inhibitors. Newer macrolide antibiotics such as azithromycin, may be associated with a reduced risk of cardiac arrhythmias. The risk related to a short course of macrolide treatment for an acute infection in a young person might be different to the risk related to prolonged use in an older patient who is more likely to both have structural cardiac disease and be taking other commonly used drugs that prolong the QT interval.

Macrolide use is the most important driver of macrolide resistance. Macrolide resistant *Streptococcus pneumoniae* is increasing in Europe. Azithromycin selects for a greater number of resistant organisms while clarithromycin selects a higher-resistance-coding gene mutation. The potential for resistance development may be greater with azithromycin compared to clarithromycin.

**Which macrolide to use:** Comparative studies of the relative clinical efficacy of different macrolide therapies have not been completed. Both azithromycin and clarithromycin are associated with increased microbial resistance. Differences in the anti-inflammatory properties are not informative as little is known about the immuno-pathophysiology of pre-school wheeze. Azithromycin has been used in the management of rhino-

sinusitis and may be associated with less cardiac conduction effects. It is for the latter two reasons that we chose azithromycin for this trial.

#### 4. STUDY OBJECTIVE

To determine if treatment of pre-school children with a history of wheeze who present to an ED with an acute wheezing episode with azithromycin for 5 days will resolve their symptoms more quickly, will use less SABA, and allow these children to remain symptom free for a longer period of time.

#### 5. HYPOTHESES

**Primary Hypothesis:** Treatment of pre-school children with an acute episode of wheezing symptoms with 5 days of azithromycin will resolve their symptoms sooner.

**Secondary Hypotheses:** Treatment of pre-school children with acute wheezing symptoms with 5 days of azithromycin will: a) cause these children to use less rescue  $\beta_2$  agonists than those treated with placebo; and b) allow these children to remain free of subsequent wheezy episodes longer than those treated with placebo.

#### 6. RESEARCH DESIGN

**Study Overview and Setting:** We propose a two arm, double blind, randomized placebo controlled trial conducted in two urban pediatric emergency departments (Alberta Children's Hospital (ACH), Calgary and Stollery Children's Hospital (SCH), Edmonton). (*Appendix A – Study Design Schema*)

**Patient recruitment:** Starting January, 2010, trained research assistants will be on-call 16 hours per day, seven days per week (*Appendix B – Emergency Medicine Research Associates Program*). The triage nurse will notify on-call research assistants about children 12-60 months of age who present with wheeze during the study period. Written, informed consent will be obtained as follows: 1) a video of a primary investigator explaining the study will be played for the parent (or legal guardian) by the assistants, 2) a primary investigator or senior research coordinator will be available by telephone to answer any questions the parent/legal guardian might have about the study 3) the research assistant will ask the parent/legal guardian who have verbally agreed to participate to sign the written consent form (*Appendix C – Consent Form*). A more lay description of the study including rationale, objectives and the study commitment will also be distributed as a brochure.

We propose to implement a lottery remuneration process within the ED. For each individual screened, the research assistant, admitting clerk, the nurse facilitating the enrollment visit can complete a ballot for entry. The ballot will contain the patient's bed number, time and date of the patient encounter. RA will check the handed ballot. The entry for RA will be confirmed through check box. The lottery draw will be completed after every 1000 entries. The winner will receive a Safeway Gift card for \$500.

**RMO Database:** We will maintain a database for eligible individuals who refuse, are missed, or are otherwise excluded to assess the generalizability of our study sample.

**Enrolment Criteria** – (*Appendix D – Patient Screening Forms*) Children 12-60 months who present to one of the participating ED and have wheeze on auscultation. Those children who had oral antibiotics during the past 30 days, those whom physician consider to provide antibiotics, those with known hypersensitivity to macrolides, those with significant comorbidities, those who are already enrolled in another study, those who does not communicate in English, those without telecommunication access, and those who are unable

to follow up in next 21 days will be excluded from the study. (*Appendix E – Detailed Inclusion and Exclusion Criteria*)

**Baseline Assessment and Patient History:** In addition to age, sex, postal code, vital signs and symptoms, a background questionnaire will be performed to document risk of multiple-trigger wheeze and asthma (i.e. wheezing/coughing in the past day and night, current and past medication usage in the last three months, other medical problems, atopic dermatitis, family history of atopy or asthma, parental smoking (*Appendix F – Patient Data Forms*)).

***Allocation, randomization, and blinding of study treatment (intervention):***

***Randomization method:*** A 2 X 2 variable blocked randomization code (ranging between 4 and 8 per block), with stratification by study site and first versus previous episode of wheeze, will be produced by the Drug Development and Innovation Centre at the university of Alberta (DDIC) using random-number generating software. DDIC will produce the study packages, complete the block randomization, and number the bottles. The blinded and numbered study drug packages, in addition to the master code will be available to both study sites if de-blinding is required. Stratification by ‘history of wheeze’ will allow us to track the number enrolled into each sub-group, and ensure we achieve our targeted sample size for each one. We have included children with both first and prior episode of wheeze and powered our study to perform a sub-group analysis for these two groups. Macrolide therapy has been shown to be effective in both bronchiolitis and asthma; incorporating both populations into this study design may provide important insights into how these populations of patients might differ.

Children will be defined as first-time wheezer if they have never had symptoms of wheeze prior to this episode, the symptoms of wheeze have been occurring for < 1 month with no period without resolution of symptoms for greater than 1 week during that 1 month period. Resolutions of symptoms include absence of all respiratory symptoms including wheeze, cough, respiratory distress, and shortness of breath. Some illustrative examples: If the patient has had symptoms for greater than 1 month- these children would be considered a repeat wheezer. If the child has had symptoms of wheezing for 1 month but had a 1 week period without respiratory symptoms in that one month, and we are seeing them after the 1 week resolution period, these children would be also be considered a repeat wheezer. IF the child has had wheezing symptoms for 1 month but was never symptoms free for more than 1 week continuously, this child would be considered a first-time wheezer.

***Blinding of azithromycin:*** The pharmacy at each site will prepare two boxes (one for children enrolled with ‘first episode of wheeze’ and the other for those with ‘prior episode of wheeze’) of sequential patient packets containing the study drug in sealed, opaque, numbered bags. Each bag will contain 2 X 10 cc syringes, and either study drug or placebo that will be indistinguishable by appearance, smell, and taste. The two boxes of patient packets (first-time wheezing patient, previous wheezing patient box) will be kept in a locked and secure room in the ED for use as patients are enrolled. The research assistant who assigns the intervention will be unaware of the next group assignment as study drugs will be packaged identically and identified only by a sequential study number.

***Randomization code access:*** The Research team from both sites will have access to the master randomization code until patient enrolment is completed and all decisions regarding statistical analyses are finalized.

**Study Intervention:** Children will be randomized to receive either azithromycin or placebo (powder to be produced by DDIC given at 10 mg/kg/day for day 1, then 5 mg/kg for 4 days. Each bottle will contain sufficient drug to adequately dose children who weigh up to 30 kg (>> 95%tile weight for 60 month old child). Excess study drug/placebo will be expelled from each syringe by the research assistant, so that the remaining volume of study drug/placebo will equal the appropriate dose based on the child's weight. An ED nurse will administer the first dose of the study drug/placebo. If the child vomits the first dose within 20 minutes of administration, a second dose will be given. The second syringe will be marked with the calculated dose level for days 2 to 5, labelled 'study drug', and provided to the parents at discharge from the ED. Parents will also be given a salbutamol metered dose inhaler (Airomir™, 100 µg per puff) fitted with a dose counter (Doser™, Meditracker), a spacer with mask (OptiChamber Advantage®, Philips Respironics), and advised to administer two puffs from the MDI via the spacer as needed, up to every four hours, if their child has symptoms of respiratory distress, wheeze, or persistent cough. Only children, who the attending ED feels would benefit from salbutamol at home, will have their salbutamol dispensed and their salbutamol usage tracked by Doser™ and by questionnaire. Children with wheeze on presentation who do not get prescribed salbutamol on discharge are still eligible for the study. As they were not prescribed salbutamol, their medication usage will not be tracked (secondary outcome). We will still track their primary outcome (time to resolution of symptoms)

**Study Drug Compliance:** Parents will also be asked to complete a daily medication diary (*Appendix G – Ordinal Daily Symptom and Drug Dosing Diary*) documenting administration of the study drug and to return the diary with the study drug bottle, MDI when they return for follow-up 21 days after enrolment. The medication diary will be reviewed and verified by the study coordinator at both telephone and in-person follow-up. If the child's respiratory symptoms are persistent for all 21 days of the calendar, a second calendar and a new MDI will be provided to the family.

**Co-Interventions and Contamination:** Staff ED physicians will be asked not to treat enrolled patients with antibiotics. Otherwise physicians will be allowed to prescribe any treatment, in addition to the study drug and rescue SABA, they judge to be necessary (e.g. oral or inhaled corticosteroids). While treatment with corticosteroids has the potential to contaminate the effects of the study medication, given our study's randomized design, each treatment group will most likely have comparable numbers of patients treated with co-interventions. All medications (including duration and dosages) patients receive at enrolment and during follow-up will be documented. A letter will also be sent to the child's primary care physician at the time of enrolment detailing the nature of the study and that the child has been randomized to either azithromycin or placebo to be taken for 5 days in total.

**Data gathering and Patient Follow-up** (*Appendix H – Data quality & monitoring*)  
**Daily Symptom Diary:** Parents will be given a Ordinal Daily Symptom Diary with the following ordered categories: heart = 'no respiratory symptoms'; green star = 'mild respiratory symptoms'; yellow star = 'respiratory symptoms are worse than usual or more medication than usual was required'; red star = 'respiratory symptoms sufficiently severe to require an unscheduled visit to a physician or treatment with oral corticosteroids' or Blue star = in addition to one of the above and a cold or flu symptoms appear. Star stickers are to be provided to place in blue boxes each day of study syrup is provided. Parents will be

instructed to focus on any noisy breathing respiratory symptom (wheezing or whistling sounds), breathlessness with eating or speaking, shortness of breath after activity or exposure to cold, or persistent troublesome coughing. (*Appendix G – Ordinal Daily Symptom and Drug Dosing Diary*). This Ordinal Daily Symptom Dairy has been used in a prior study by PM with excellent parental and child compliance, and good discrimination in respiratory symptoms between treatment groups (Montelukast versus placebo).

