***Safety monitoring committee and termination policy:*** Adverse events will be actively monitored up to 30 days after the last of Azithromycin was given (day 5). Any child who develops symptoms consistent with adverse effects to azithromycin as evidenced by diarrhea or loose stools, nausea, abdominal pain, and vomiting (common side effects), symptoms of allergic reaction (hives), changes in mood or behaviour, arrhythmia/tachycardia will result in the review of their case by a safety monitoring committee consisting of a pediatric pulmonologist, allergist, and general pediatrician. The committee will review the case and decide whether to break the code and/or terminate the study based on the particulars of the case. If upon review there are concerns about the patient, the code would be broken and the randomization drug discontinued. The panel may consider terminating the study if there are profound adverse effects that would reflect concerns for all children.

***Sample Size and Minimal Clinically Important Difference:*** The telithromycin in acute adult asthma study demonstrated a 50% reduction in asthma symptoms among those using telithromycin (16% asthma symptoms in the placebo group versus 8% in the telithromycin group). We have used this data to estimate the magnitude of effect for our sample size calculations (a 50% decrease in the number of days to symptom resolution). Enrolment of 110 children per treatment arm per first-time versus previous wheeze (total 440), using a one-way ANOVA, will provide 80% power to detect at the .05 level, a 1.18 day

differences in the two treatment groups. This calculation assumes a conservative standard deviation of 6 days in symptoms duration and a 10% loss to follow-up. For the planned sub-group analysis of first-time versus previous wheeze, we have sufficient power to detect a 1.36 day difference between the azithromycin and placebo groups (*Appendix M – Power Calculation*). We think that a reduction in the duration of symptoms by one day or more is likely to be considered meaningful because of its implication for a child missing daycare or school, or parents missing work.

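### Stratified randomisation cannot secure the target size of each wheeze-history sub-group; the plan states no quota or closing rule, and its 1.36-day sub-group figure fails even at 220:220

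*Protocol*

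**What the plan says.** Under Randomization method (Section 6), the code uses variable blocks of 4 to 8 "with stratification by study site and first versus previous episode of wheeze". The same paragraph says of stratifying on wheeze history that it "will allow us to track the number enrolled into each sub-group, and ensure we achieve our targeted sample size for each one", and that the study is powered for a sub-group analysis in both groups.

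The paragraph on sample size gives the target: "Enrolment of 110 children per treatment arm per first-time versus previous wheeze (total 440"). It says that this "will provide 80% power to detect at the .05 level, a 1.18 day" difference overall. On the inputs it says: "This calculation assumes a conservative standard deviation of 6 days in symptoms duration", with "a 10% loss to follow-up". For the comparison within first-time and previous wheezers it adds that "we have sufficient power to detect a 1.36 day difference".

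On recruitment, Section 6 says: "The triage nurse will notify on-call research assistants about children 12-60 months of age who present with wheeze during the study period". Under Blinding of azithromycin, each site holds two boxes of numbered packets, one per wheeze-history group. No packet limit is given. The enrolment criteria in the main text do not depend on wheeze history. The text available gives no expected mix, no cap on a stratum, and no rule on what happens when one stratum fills before the other.

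**The concern.** The property claimed does not come from the mechanism named. Stratified blocking fixes the ratio of the two treatments inside each site-by-history cell. It leaves the number of children in each cell free. Tracking the numbers would show a shortfall but would not prevent one.

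This matters because the Statistical Analysis paragraph plans a placebo-versus-azithromycin comparison in each history group, and the sample-size paragraph gives a single detectable difference for both. That single figure presupposes two strata of 220. If one stratum ended well short, its comparison would be weaker than stated, and a null result there could be read as no effect in that type of wheezer.

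**Working it through.** **Inputs.** From the Protocol: 440 enrolled, 110 per arm per stratum, 10% loss, SD 6 days, level 0.05, power 80%. Assumed here: a two-sided test (sidedness is not stated), 80% power for the sub-group claim as well (not restated there), and the stratum mix (not given).

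**Formula.** For two means with n evaluable per arm, detectable difference = (1.960 + 0.842) × SD × √(2/n). This is the normal approximation; the two-sample t-test gives slightly larger values.

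**1. The plan's own sub-group figure.**

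- Evaluable per arm per stratum at 220:220: 110 × 0.9 = 99.
- Detectable difference: 2.802 × 6 × √(2/99) = 2.39 days (2.40 by t-test). The plan says 1.36.
- Without the 10% loss (110 per arm): 2.27 days. One-sided: 2.12 days (99 per arm) or 2.01 days (110 per arm). None of these gives 1.36.
- Power for 1.36 days with 99 per arm: the standard error is 6 × √(2/99) = 0.853, so 1.36/0.853 = 1.595, and Φ(1.595 − 1.960) = about 36%. It is 39% with 110 per arm.
- Number needed for 1.36 days: 2 × 2.802² × 6² / 1.36² = 306 evaluable per arm, or 306/0.9 = 340 enrolled per arm, in each stratum.
- The two stated figures also disagree with each other. Halving n at the same SD multiplies the detectable difference by √2, which takes 1.18 to 1.67, not 1.36.

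The 1.36-day claim therefore fails on the plan's own inputs before any question of mix arises.

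**2. Effect of the mix, if enrolment stopped at 440.** Evaluable per arm in the smaller stratum = 440 × share / 2 × 0.9.

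| Share of smaller stratum | Children | Evaluable per arm | Detectable difference, t-test (normal) | Power for 2.40 days | Power for 1.36 days |
|---|---|---|---|---|---|
| 50% | 220 | 99 | 2.40 (2.39) | 80% | 36% |
| 40% | 176 | 79.2 | 2.69 (2.67) | 71% | 30% |
| 30% | 132 | 59.4 | 3.11 (3.08) | 58% | 23% |

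The relative loss does not depend on the SD. The detectable difference grows by √(50/40) = 1.12 and √(50/30) = 1.29. Taking the plan's claim at face value (80% power for 1.36 days with 99 per arm, which implies an SD of about 3.42), power in the smaller stratum still falls from 80% to 71% and 58%.

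**3. What a closing rule does to the total.** If each stratum closes at 220, the total stays at 440. If the commoner stratum is left open until the rarer one reaches 220, the total is 220/0.40 = 550 at a 40% share and 220/0.30 = 734 (rounded up) at a 30% share.

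**The case against.** The strongest reply is that the protocol already implies the right rule. The target is set per stratum and 440 is only its sum. Numbers in each group are to be tracked, and each group has its own box of packets. All of this fits filling each stratum to 220. Nowhere does the protocol say that enrolment stops at 440 whatever the mix. A closing rule could also sit in the screening forms, the detailed criteria or the power calculation (Appendices D, E and M), which are cited but not available here. Nor is an exact 220:220 split critical: at 45:55 the smaller stratum's detectable difference is only about 2.53 days.

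Most of this stands. A reader might infer that the mix is bound to follow the emergency department's case mix and that the rarer group will fall short. The documents do not support that. The recruitment text has the triage nurse notify research assistants, and notification does not commit the trial to enrolling every child or stop it from closing a full stratum. The documents also do not say which group is rarer, or by how much.

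What does not stand is the causal statement itself. Whatever the appendices contain, stratification does not secure stratum size, and the rule that would do so is left unstated in the main text.

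**Conclusion.** The point holds as a wrong attribution and an unstated rule. It does not show that the design will miss its sub-group targets. If enrolment stopped at 440 with an uneven mix, the smaller stratum's detectable difference would go from 2.40 days to 2.69 (40:60) or 3.11 (30:70). Both the stop at 440 and those mixes are assumptions.

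A reader might also conclude that an uneven mix is what breaks the sub-group power, so that equal strata would restore it. The plan's figures do not support this. At an exact 220:220 split the power for 1.36 days is about 36% (two-sided 0.05, SD 6, 10% loss). An uneven mix makes an existing shortfall worse, and a closing rule alone would leave the 1.36-day claim uncorrected.

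**What to change.** In Randomization method, remove the statement that stratification secures the size of each sub-group. Then state one of two rules:

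- **(a)** Each wheeze-history stratum closes at 220 children (110 per arm) while the other stays open. The total stays at 440. The cost is a real change to enrolment and possibly longer recruitment in the rarer stratum.
- **(b)** Recruitment stops at 440 in total and the split follows presentation. The cost is a less favourable stated figure for the smaller stratum.

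Under either rule, replace the 1.36-day figure in the sample-size paragraph and in Appendix M. Under (a) the recomputed sub-group detectable difference is about 2.4 days in each stratum. Under (b), give the expected split and a figure for each stratum at that split. State the sidedness and the power that the sub-group figure assumes. This part is a recalculation and a change of wording.
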